#### Statistical methods

There are two main approaches to the analysis of cluster-randomized trials: cluster-level analysis or regression analysis of individual-level observations that take into account intracluster correlation [15]. Individual-level regression methods are more statistically efficient and allow for the presentation of the effects of modeled covariates alongside intervention effects, but this approach may not be robust when there are a relatively small number of clusters per arm. Therefore, we will conduct both individual-level and cluster-level analyses.

##### Cluster-level summaries

To determine if there is a statistically significant difference in the proportion of INH prescriptions among IPT-eligible patients between treatment and control clusters, we will use an unpaired *t*-test. We will also estimate the relative risk of INH prescription and associated 95% confidence intervals. We will use Kaplan–Meier methods to calculate the proportion of eligible patients receiving INH prescriptions within 3 months of their initial encounters. To test the null hypothesis that there is no difference between the survival curves, we will use the log rank test.

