#### Treatment group specification and assignment

Clusters will be sorted into four strata and randomly assigned to the treatment or control group with an allocation ratio of 1:1. The two stratifying variables will be average monthly patient volume and the percentage of initial patient encounters in 2013 with CXR results recorded in AMRS. Stratifying on cluster size is advantageous when cluster sizes vary in the population and when cluster size might be correlated with the endpoint of interest [14]. Stratifying on the availability of CXR results in AMRS will potentially reduce the imbalance on a cluster-level covariate that we expect will be related to isoniazid (INH) prescribing behavior.

AMPATH clinical protocols advise that all patients should have a normal CXR that is no more than 6 months old before medical providers prescribe IPT (assuming no other contraindications). However, in 2013, fewer than a third of initial encounters with HIV-positive adults had CXR results recorded in AMRS. When results are missing from AMRS, CDSS will print a general reminder about ordering a CXR. At best, a general reminder that prints for most patients will potentially lead to reminder fatigue. At worst (when CXR results exist and are known to the provider), the prompt to order a CXR is a false positive; in these cases, the summary sheet should contain a more specific reminder about considering anti-TB treatment or IPT based on the CXR result and patient symptoms, not a reminder to order a CXR. We expect the general reminder to order a CXR, particularly where the printing of this reminder is a false positive, to be less impactful on INH prescribing behavior. We also expect these messages to be more common at facilities that are less successful in entering CXR results into AMRS. Therefore, we will stratify randomization on baseline facility-level availability of CXR results in AMRS.

Both stratifying variables will be dichotomized (volume greater than 1,000 patients per month and percentage of results in AMRS greater than 23%) to create four possible strata: low volume/low results; low volume/high results; high volume/low results; high volume/high results.

Clinical summary sheets for patients receiving care at treatment clusters will include the new TB care reminders (as needed) *plus* the full set of existing reminders, whereas summary sheets printed at control clusters will only include the existing set of reminders (i.e., no new TB care reminders).

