#### Statistical design considerations

This will be a pragmatic, parallel-group, cluster-randomized superiority trial with a 1:1 allocation to treatment ratio from within four strata. Assuming a desired power of 0.80, alpha of 0.05, 20 clusters equally allocated to treatment and control, 50 patients per cluster, a between-cluster coefficient of variation of 0.25 and a baseline INH prescription rate of 15%, we will be able to detect a minimum shift of almost 8 percentage points in the INH prescription rate, from 15% to almost 23% using a one-tailed test^e^.

Based on a recent retrospective review of AMRS data, we believe that the current rate of INH prescription is between 5% and 25%. Historically, this rate was higher at nearly 40%. No matter where the true baseline rate is in this range, our minimum detectable effect is not projected to rise above 8 percentage points, if everything else is held constant.

The between-cluster coefficient of variation is also important in this calculation. Without cluster-level baseline data on the INH prescription rate, we have to estimate. This variation is often less than 0.25 and rarely exceeds 0.50 [15]. In the previous calculations, we set the between-cluster variation to be 0.25 and scaled it down by 0.75 to account for the benefits of stratification. If the between-cluster variation is really at the high end of this range before scaling (0.50), then the minimum detectable effect climbs to almost 12 percentage points. If we further assume that it is only possible to observe half as many patients per cluster (25), the minimum detectable effect increases to 14 percentage points.

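### The detectable differences take credit for stratification, but the unpaired t-test named for the proportion ignores the strata and does not deliver the stated 80% power

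*Protocol article*

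**What the plan says.** Three parts of the protocol article bear on this point.

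- **Randomisation** (Treatment group specification and assignment): "Clusters will be sorted into four strata and randomly assigned to the treatment or control group". The strata come from dichotomising monthly patient volume and the share of initial encounters with a chest radiograph result in the record system. The protocol expects the second factor to be related to prescribing.
- **Power** (Statistical design considerations): "Assuming a desired power of 0.80, alpha of 0.05, 20 clusters equally allocated to treatment and control, 50 patients per cluster", with a CV of 0.25 and a 15% baseline, gives a detectable shift "from 15% to almost 23% using a one-tailed test". On the CV, the protocol says "we set the between-cluster variation to be 0.25 and scaled it down by 0.75 to account for the benefits of stratification". A CV of 0.50 before scaling gives just under 12 points, and halving the cluster size to 25 as well gives 14. Endnote e cites a formula for stratified cluster-randomised trials.
- **Test** (Cluster-level summaries): for a difference "in the proportion of INH prescriptions among IPT-eligible patients between treatment and control clusters, we will use an unpaired" *t*-test. The strata are not mentioned.

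Under Statistical methods, both cluster-level and individual-level analyses are planned and neither is ranked first. The individual-level section says that random-effects logistic and GEE models will be evaluated. It gives age, gender and CD4 count as examples of individual-level covariates.

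**The concern.** Stratifying the randomisation makes the arms more alike, so the true variance of the treatment contrast falls. A test gains from this in its standard error only if it removes the between-stratum variance. An unpaired *t*-test estimates its variance from all clusters within each arm, so differences between strata stay in the denominator. The power calculation assumes they have been removed.

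The risk is a missed effect and not a false positive. The test runs below its nominal level, its confidence interval is wider than it need be, and its power at the stated differences is below 80%. With 20 clusters there is little to spare, and the protocol itself looks ahead to the interpretation of a null result.

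**Working it through.** **Inputs** (all from Statistical design considerations): power 0.80; one-tailed alpha 0.05; 10 clusters per arm; m = 50 (25 in the last scenario); p0 = 0.15; CV k = 0.25 or 0.50, scaled to 0.1875 or 0.375.

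**Step 1. Reproduce the stated figures.** The cluster-trial formula for proportions is

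c = 1 + (z_α + z_β)² × [p0(1−p0)/m + p1(1−p1)/m + k²(p0² + p1²)] / (p1−p0)².

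With c = 10 and (1.645 + 0.842)² ≈ 6.18, this becomes d² = 6.18 × [bracket] / 9.

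Base case, k = 0.1875, p1 = 0.2272: bracket = 0.00255 + 0.00351 + 0.00261 = 0.00867, so d = √(6.18 × 0.00867/9) ≈ 0.0772.

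**Step 2. Remove the 0.75 factor.** With k = 0.25 and p1 = 0.2373: bracket = 0.00255 + 0.00362 + 0.00493 = 0.01110, so d ≈ 0.0873.

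| Scenario | Stated | With 0.75 | Without 0.75 |
|---|---|---|---|
| CV 0.25, m = 50 | just under 8 | 7.72 | 8.73 |
| CV 0.50, m = 50 | just under 12 | 11.59 | 15.74 |
| CV 0.50, m = 25 | 14 | 13.93 | 17.89 |

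With this one-tailed formula, all three stated figures come back with the scaled CV and none without it.

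**Step 3. What the factor implies.** The share of between-cluster variance explained by strata is 1 − 0.75² = 0.4375, about 44%.

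**Step 4. Unpaired test after stratified randomisation.** If that share is right, the contrast has the smaller standard error (SE_w, scaled k), but the test uses the larger one (SE_t, unscaled k):

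power = Φ[(d − 1.645 × SE_t) / SE_w].

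Base case at d = 0.0772:
- SE_w = √(0.00867/9) = 0.0310
- SE_t = √(0.01069/9) = 0.0345
- power = Φ[(0.0772 − 0.0567)/0.0310] = Φ(0.66) ≈ 75%

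CV 0.50 at d = 0.1159:
- SE_w = 0.0466 and SE_t = 0.0575
- power = Φ[(0.1159 − 0.0946)/0.0466] = Φ(0.46) ≈ 68%

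CV 0.50 with m = 25, at 13.9 points: about 70%.

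Solving for 80% power gives detectable differences of 8.4, 14.2 and 16.4 points. The actual one-sided type I error is about 3.7% in the base case and 2.5% at CV 0.50 with m = 50.

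**Step 5. Simulation.** 60,000 runs, 20 clusters, strata explaining 44% of between-cluster variance, stratum sizes 4/6/4/6 (assumed). The unpaired test has 18 df. The linear model with arm and stratum has 15 df (20 − 1 − 4).

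| True difference | Unpaired | Stratum-adjusted |
|---|---|---|
| 0 (CV 0.25) | 3.7% | 5.1% |
| 7.72 points (CV 0.25) | 75% | 81% |
| 11.59 points (CV 0.50, m = 50) | 69% | 82% |
| 13.93 points (CV 0.50, m = 25) | 73% | 82% |

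A separate rerun put the unpaired test at about 77% and 72% in the second and third rows, hence the ranges 75–77% and 68–72%. Four different stratum layouts moved power by no more than about 1 point.

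**Step 6. If the strata explain less.** CV 0.25, 7.72 points, 20,000 runs, sizes 6/4/4/6 (assumed):

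| Share explained by strata | Unpaired | Stratum-adjusted |
|---|---|---|
| 0 | 74% | 73% |
| 0.1 | 74% | 75% |
| 0.2 | 74% | 77% |
| 0.4375 | 75% | 81% |

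**The case against.** The strongest reply is that this is a condensed article, and the way strata enter a model is commonly left to the full analysis plan. That would answer a mere silence. Here the article names one test and a power figure that presupposes another, so the mismatch is in the text itself.

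Three stronger readings are tempting, and the document does not support them.

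- **That the primary analysis ignores the strata.** The *t*-test is not labelled primary. Cluster-level and individual-level analyses are both planned without ranking, and the individual-level methods are described as the more efficient. What can be said is that the *t*-test is the only specific test fixed for the proportion, which is the subject of the primary hypothesis.
- **That the regression models leave the strata out.** The covariate list is illustrative and concerns individual-level covariates. The stratifiers are facility-level, so their absence from the list shows nothing.
- **That the real detectable difference is 8.7 points.** That figure gives stratification no credit at all. If the strata work as the protocol assumes, stratified randomisation still lowers the true variance, and the unpaired test detects about 8.4 points.

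Two further replies stand in part. The base-case loss is modest and no false-positive risk arises. The loss also depends on the 0.75 factor, for which the protocol has no cluster-level baseline data: if the strata explain little, a stratum-adjusted test does not reach 80% at 7.7 points either (step 6).

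**Conclusion.** The concern holds as a mismatch between the power calculation and the one specific test named for the proportion. Under the protocol's own assumption about the strata, the unpaired test falls short of 80% power by about 3 to 5 percentage points at a 7.7-point difference (CV 0.25), and by about 8 to 12 at 11.6 points (CV 0.50, the high end that the protocol considers). The base-case detectable difference rises from 7.7 to about 8.4 points. The test is conservative, so its validity is not in question.

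The result rests on the 44% share implied by the 0.75 factor, on assumed stratum sizes (which matter little), and on a one-tailed test as in the power calculation.

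**What to change.** Under Cluster-level summaries, replace the unpaired *t*-test with a stratum-adjusted cluster-level test: a stratified *t*-test, or a linear model of the 20 cluster proportions on arm and the four-level stratum with 15 df. State that the strata also enter the random-effects, GEE and Cox models.

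This changes wording only and needs no new data. It costs three degrees of freedom, with a slight loss of power if the strata explain little variance (73% against 74% at a share of zero). It should be settled before outcomes are analysed.

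If the unpaired test is kept, restate the detectable differences and the premise behind them. They are about 8.4 points in the base case (14.2 and 16.4 in the other two scenarios) if stratified randomisation lowers the true variance as assumed. They are 8.7, 15.7 and 17.9 points if the 0.75 factor is dropped.

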##### Individual-level regression analysis

In addition to the analyses based on cluster-level summaries, we will also use regression models with individual-level data that account for between-cluster variation. Specifically, we will evaluate the reliability of logistic regression random effects models and generalized estimating-equation approaches to model our binary outcome. We will use Cox regression with random effects to model the time to INH prescription. Individual-level covariates will be limited to data collected reliably in AMRS, such as age, gender and CD4 count.

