#### Subset analyses

Previous research in the AMPATH network suggests that IPT initiators are more likely to be younger, female and have a higher CD4 count. We will dichotomize each variable and test for differing intervention effects in each subgroup. We will also test the hypothesis that patients with a greater number of reminders printed on each summary sheet will be less likely to initiate IPT compared to patients with fewer reminders. It is possible that each additional reminder increases the cognitive demand on a provider and makes it more likely that the provider will ignore the reminders.

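### The cluster-level t-test, kept for robustness with few clusters, is valid but has no covariate-adjusted version, so precision available from age, gender and CD4 count goes unused

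*Protocol article*

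**What the plan says.** The Statistical methods section of the protocol article sets out two routes. Individual-level regression is described as more efficient and able to carry covariates, with the caution that "this approach may not be robust when there are a relatively small number of clusters per arm". It concludes: "Therefore, we will conduct both individual-level and cluster-level analyses". Neither route is named as the decisive one.

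Under Cluster-level summaries, the proportion prescribed isoniazid is compared "between treatment and control clusters, we will use an unpaired" *t*-test. No covariate is mentioned.

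Under Individual-level regression analysis: "Individual-level covariates will be limited to data collected reliably in AMRS, such as age, gender and CD4 count". Under Subset analyses, earlier work in the same network is reported to show that "IPT initiators are more likely to be younger, female and have a higher CD4 count". No odds ratio is given for any of the three variables, nor how far they vary between clusters.

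**The concern.** Read together, these sections apply the known predictors of the outcome only in the analysis whose small-sample behaviour the article doubts. The analysis added as a safeguard uses none of them. Efficiency with covariates is set against robustness without them, but the choice is not forced. A two-stage cluster-level test adjusts for patient covariates and still treats the cluster as the unit of analysis.

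Two things are at stake. The first is precision: with 10 clusters per arm, chance differences in patient mix add noise to the raw comparison, and covariates could remove some of it. The article reports that only 22 facilities met the criteria and 20 are used, so there is little room to gain precision by adding clusters. The second is interpretation: an adjusted regression and a raw *t*-test differ in both method and covariates, so a disagreement between them has two possible causes.

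**Working it through.** **1. The plan's own figure.** Inputs from Statistical design considerations: "Assuming a desired power of 0.80, alpha of 0.05, 20 clusters equally allocated to treatment and control, 50 patients per cluster". The test is one-sided and the control rate is 15%. The coefficient of variation (0.25) is also reduced: the authors "scaled it down by 0.75 to account for the benefits of stratification", so k = 0.25 × 0.75 = 0.1875. The article cites its equation without printing it. The standard cluster-level form is

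c = 1 + (z_α + z_β)² × [p0(1−p0)/m + p1(1−p1)/m + k²(p0² + p1²)] / (p1 − p0)².

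With c = 10, m = 50, p0 = 0.15 and (1.645 + 0.842)² ≈ 6.18, try p1 = 0.2272:

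- within-cluster part: 0.1275/50 + 0.1756/50 = 0.00606
- between-cluster part: 0.03516 × (0.0225 + 0.0516) = 0.00261
- total 0.00867; 1 + 6.18 × 0.00867/0.0772² ≈ 10.0

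The detectable difference is 7.72 points, against the stated figure of almost 8. The same formula gives 11.59 points (k = 0.50 × 0.75 = 0.375) and 13.93 points (that k, 25 patients per cluster), against almost 12 and 14. All three figures reproduce with no covariate term.

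**2. Where covariates could help.** At these values the within-cluster part is 0.00606/0.00867 = 70% of the variance of a cluster proportion and the between-cluster part is 30%. Suppose adjustment removes a share Rb of the between-cluster part and Rw of the within-cluster part (assumed, since the article gives neither):

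| k | Rb | Rw | Power | Detectable difference |
|---|---|---|---|---|
| 0.1875 | 0 | 0 | 80.0% | 7.72 |
| 0.1875 | 10% | 0 | 81.1% | 7.58 |
| 0.1875 | 25% | 0 | 82.7% | 7.39 |
| 0.1875 | 50% | 5% | 86.6% | 6.89 |
| 0.375 | 0 | 0 | 80.0% | 11.59 |
| 0.375 | 10% | 0 | 82.4% | 11.08 |
| 0.375 | 25% | 0 | 86.0% | 10.30 |

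Each power is taken at the difference detectable without adjustment for that k.

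**3. Simulation by odds ratio.** 20 clusters of 50, 15% v 23%, three binary covariates, and case-mix variation between clusters from none to strong (1,500 runs per setting, Monte Carlo SE about 0.9 points). Power, raw then adjusted:

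- odds ratio 1.3 each: 84–86% then 85%
- odds ratio 1.5 each: 81–87% then 84–87%
- odds ratio 2.0 each: 82–85% then 86–87%

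The gain runs from about −0.5 (noise) to +5 points. The +5 needs odds ratios of 2.0 and strong case-mix variation.

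**4. Simulation with the total between-cluster coefficient of variation held at 0.1875 or 0.25.** Here 2–10% of covariate variance lies between clusters. Covariate strength is the SD of the combined log-odds. For three evenly split binary covariates this is ln(OR) × 0.5 × √3, so SD 0.3 is an odds ratio of about 1.4 on each and SD 0.6 about 2.0 on each.

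| Combined log-odds SD | Change in power | Fall in variance |
|---|---|---|
| 0.3 | about 0 to +2 points | 3–9% |
| 0.6 | about +1 to +7 points | 7–25% |

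The false-positive rate was 4.5% adjusted v 4.8% raw. The adjusted difference was pulled towards zero by about 0.1–0.2 point, because arm is left out of the first stage.

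**5. What the top of the range requires.** At SD 0.6 with 10% of covariate variance between clusters, case mix contributes 0.36 × 0.10 = 0.036 to the between-cluster variance on the logit scale. The total there is (0.1875/0.85)² = 0.0487. Case mix would thus account for 0.036/0.0487 = 74% of all variation between clusters. That is a demanding assumption, so +7 is an upper end and not an expectation.

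**The case against.** The strongest reply is that nothing here is wrong. An unpaired *t*-test on cluster proportions is a sound analysis for 10 clusters per arm, adjustment is already planned in the parallel regressions, and the article openly presents the pair as a trade-off. Most of this stands, and it rules out four stronger readings that a reader might infer.

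- *That chance imbalance biases or invalidates the raw test.* It does not. Under randomisation the standard error covers chance imbalance, and the simulated raw false-positive rate is close to 5%.
- *That planned power is lost.* The 80% figure reproduces without covariates, so what is missed is an unclaimed gain.
- *That case mix is left unaddressed.* The regressions may adjust for it. What is missing is an adjusted version of the robust analysis.
- *That a disagreement between the two analyses could not be explained.* Fitting the regression without covariates would also separate case mix from method failure, and the article undertakes to assess the reliability of its models.

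The size of the gain also rests on covariate strengths that the article does not give. With weak covariates it is within simulation noise.

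One part of the reply does not stand: that this is detail left to an analysis plan. The article names the cluster-level test and assigns the covariates to the other route, so this is a stated choice, and a better one is available at little cost.

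**Conclusion.** The point holds as an improvement to a valid analysis. The cluster-level *t*-test has no adjusted counterpart, although the article calls three covariates reliable and relates them to starting preventive therapy. For a combined log-odds SD of 0.3 to 0.6, the forgone gain is about 0 to 7 power points and a variance about 3–25% lower, with type I error controlled. The range assumes 50 patients per cluster, complete covariates, a total between-cluster coefficient of variation of 0.1875 or 0.25, and up to 10% of covariate variance between clusters. By formula, the gain is larger if the coefficient is nearer 0.375 and case mix explains much of it. The documents do not allow a single figure, and the stated power does not depend on one.

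**What to change.** Pre-specify a two-stage cluster-level test, before outcomes are compared by arm:

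1. Fit a logistic regression of isoniazid prescription on age, gender and CD4 count at the initial encounter, leaving out arm.
2. For each of the 20 clusters, take the observed minus the expected proportion, and compare these residuals between arms with the *t*-test. The covariates are at patient level, so the test keeps 20 − 2 = 18 degrees of freedom.
3. Report the raw *t*-test beside it.
4. State a simple rule for missing CD4 counts, such as a missing-value category.

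The cost is a few sentences and a few lines of code on data already in the record system. The downsides are the missing-CD4 rule, since the article does not say how complete CD4 is at the initial encounter, and the attenuation of about 0.1–0.2 point. Fixing the choice in advance matters because an adjusted test added later could look selective.

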### Study population

#### Medical facilities

Medical providers with responsibility for diagnosing TB and prescribing TB medication and IPT will be the intervention targets for this study. Due to logistical challenges of provider randomization and concerns about spillover between medical personnel exposed to TB reminders and personnel in the no TB reminders control group, medical facilities rather than individual providers will be randomized to the treatment and control groups.

To be included in the study as a cluster, a facility had to meet the following criteria:
active operations as an HIV Care Clinicuses AMPATH HIV initial and return encounter forms (paper)enters data into AMRS or sends forms to central location for data entryprints or receives printed paper clinical summary sheets with remindersprescribes IPTclassified as a mother facility in the AMPATH network^a^

There are currently 22 AMPATH facilities that meet these criteria. We decided to exclude two facilities to bring the total number of study clusters to 20: a facility that operates as a regional referral hospital and a small facility that is very new to the network.

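### The log rank test planned for time to INH prescription makes no stated allowance for clustering by facility, so at the plan's own inputs its false-positive rate exceeds the nominal 5%

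*Protocol article*

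**What the plan says.** The protocol article's secondary hypothesis is directional: patients at treatment clusters should reach INH prescription sooner. Under Cluster-level summaries, Kaplan–Meier methods are used "to calculate the proportion of eligible patients receiving INH prescriptions within 3 months of their initial encounters", and then "To test the null hypothesis that there is no difference between the survival curves, we will use the log rank test". No clustered, stratified or permutation version is named, and it is the only test of time under that heading.

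The section Medical facilities fixes the unit of allocation: "medical facilities rather than individual providers will be randomized to the treatment and control groups". The Statistical methods section names two main approaches to such trials: "cluster-level analysis or regression analysis of individual-level observations that take into account intracluster correlation". It cautions that individual-level regression may be unreliable with few clusters per arm, and for that reason adopts both approaches.

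Two other sections bear on the point. Individual-level regression analysis adds a Cox model with random effects for time to prescription. Endpoints builds the time endpoint by averaging per-cluster mean delays within each arm. No section says which time analysis decides the hypothesis.

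**The concern.** A log rank test compares patients' event times, and its standard variance treats those patients as independent. Listing it under a cluster-level heading does not change that. Patients at one facility share prescribers, chest radiograph availability and local habits, so the two arms would differ by chance more than the test allows for.

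The test therefore fits neither of the two approaches the plan describes. It also falls where the plan looks for protection: the cluster-level analysis is there because regression may be fragile with ten clusters per arm, and for time that analysis is a patient-level test. Shortening the time to IPT is part of the main research question, so a positive claim could come from facility-to-facility variation alone.

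**Working it through.** **Inputs**, all from Statistical design considerations:
- "Assuming a desired power of 0.80, alpha of 0.05, 20 clusters equally allocated to treatment and control, 50 patients per cluster", with 25 per cluster as a pessimistic case.
- "a between-cluster coefficient of variation of 0.25 and a baseline INH prescription rate of 15" per cent. On the range of the CV: "This variation is often less than 0.25 and rarely exceeds 0.50".
- The CV is multiplied by 0.75 for stratification: 0.25 × 0.75 = 0.1875 and 0.50 × 0.75 = 0.375.
- The sizing is one-tailed. The sidedness of the log rank test is not stated, so both are shown.

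**Step 1: reproduce the plan's figures.** Solve for p1 with c = 10 clusters per arm:

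c = 1 + (z_α + z_β)² [p0(1−p0)/m + p1(1−p1)/m + k²(p0² + p1²)] / (p1−p0)²

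With one-sided α of 0.05, power 0.80 and the scaled CV, the detectable differences are 7.72 points (k = 0.25, m = 50), 11.59 (k = 0.50, m = 50) and 13.93 (k = 0.50, m = 25). The plan states almost 8, almost 12 and 14. The form of the equation was chosen as the variant that reproduces all three, so the inputs are being read as the plan used them.

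**Step 2: size of a test that ignores clustering.**
- ICC = k²p/(1−p)
- Design effect DE = 1 + (m−1) × ICC
- One-sided size = 1 − Φ(1.645/√DE)
- Two-sided size = 2[1 − Φ(1.96/√DE)]

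For k = 0.25, p = 0.15, m = 50: ICC = 0.0625 × 0.15/0.85 = 0.0110, and DE = 1 + 49 × 0.0110 = 1.54.

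| CV (p = 15%, m = 50) | ICC | DE | One-sided size | Two-sided size |
|---|---|---|---|---|
| 0.1875 (0.25 scaled) | 0.0062 | 1.30 | 7.5% (1.5×) | 8.6% (1.7×) |
| 0.25 | 0.0110 | 1.54 | 9.3% (1.9×) | 11.4% (2.3×) |
| 0.375 (0.50 scaled) | 0.0248 | 2.22 | 13.5% (2.7×) | 18.8% (3.8×) |
| 0.50 | 0.0441 | 3.16 | 17.7% (3.5×) | 27.0% (5.4×) |

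With 25 patients per cluster and CV 0.25 to 0.50, the multiples are 1.4 to 2.5 one-sided and 1.6 to 3.4 two-sided. Over the plan's baseline range of 5% to 25%, with m = 50 and the same CVs, they run from 1.3 to 4.7 one-sided and 1.4 to 7.7 two-sided.

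**Step 3: simulation of the log rank test itself.** Each setting had 4,000 trials with no effect, 20 clusters, beta-distributed cluster rates, and exponential times censored at 90 days.

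| CV (p = 15%, m = 50) | Log rank, one-/two-sided | t-test on cluster proportions, one-/two-sided |
|---|---|---|
| 0 | 5.4% / 5.3% | 5.6% / 6.0% |
| 0.1875 | 7.5% / 8.7% | 5.1% / 5.3% |
| 0.25 | 8.9% / 11.4% | 4.9% / 4.6% |
| 0.375 | 13.1% / 19.1% | 4.4% / 4.7% |
| 0.50 | 16.8% / 26.3% | 5.1% / 5.3% |

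The log rank test is close to 5% without between-cluster variation and inflates in line with Step 2 once there is some. A cluster-level t-test on the same data stays near 5%. Under an assumed cluster-size CV of 0.6, which is not a figure in the protocol, the two-sided log rank size rises to 13.8% at CV 0.25 and 30.7% at CV 0.50.

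**The case against.** The strongest reply is that the plan does not rest on the log rank test alone. A reader might infer that its p-value by itself decides the secondary hypothesis, or that time to prescription has no cluster-adjusted analysis. The document supports neither: the random-effects Cox model addresses the same outcome and allows for between-cluster variation. This stands as mitigation. It is not a cure, because the plan doubts that class of model with few clusters and gives it no precedence.

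Second, the Statistical methods section describes two main approaches; it does not lay down a requirement. That is right, so the fault is that the log rank test fits neither approach the plan adopts, not that it breaks a stated rule.

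Third, this is a condensed article, and a clustered log rank version is not expressly excluded. That has limited force: the sentence names the standard test, applied to curves of eligible patients.

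Fourth, a single multiple of two to five would overstate what is known. It needs a two-sided test, a 15% baseline, 50 patients per cluster and the unscaled CV. The hypothesis is directional and the sizing one-tailed, and both the scaled CV and smaller clusters lower the figure. This stands, and the multiple should always be given with its conditions.

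**Conclusion.** The point holds in this limited form. The only test of time under Cluster-level summaries is a pooled-patient log rank test with no stated allowance for clustering. At a 15% baseline, 50 patients per cluster and CV 0.25 to 0.50, its actual size is about 11% to 27% two-sided or 9% to 18% one-sided. If stratification removes as much between-cluster variation as the 0.75 factor assumes, it is about 9% to 19% two-sided or 7.5% to 13.5% one-sided. In every setting examined with between-cluster variation, the test rejects too often.

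The size rests on the plan's assumed CV, since it has no cluster-level baseline data, and on reading the log rank test as the ordinary one. A reader might extend the criticism to the primary comparison. The document does not support that: the unpaired t-test on prescription proportions sits under the same heading, can be read as a test on cluster proportions, and on that reading keeps its size.

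**What to change.** Replace the ordinary log rank p-value with one valid at the unit of randomisation, by either route:

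1. Compute a time summary per cluster, for example restricted mean time to prescription over 90 days, and compare arms with a cluster-level t-test. This agrees with the cluster-mean form of the time endpoint. Comparing cluster Kaplan–Meier proportions at day 90 would be a poorer choice, because it largely repeats the primary endpoint and says little about speed.
2. Keep the log rank statistic, but take its p-value from permuting whole-cluster assignments within the four randomisation strata.

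State whether this analysis or the random-effects Cox model decides the secondary hypothesis, and whether the test is one- or two-sided. The Kaplan–Meier curves can stay as description.

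The cost is analysis wording only, with no change to design, data collection or conduct. The p-value for time will usually be less favourable.
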